## 2 STUDY OBJECTIVE

**AIM 1:** Use EHR data to inform primary care outpatient clinics of older adults who are at high risk of falls due to the chronic use of opioids and/or BZDs. Once alerted, clinics will use a team-based approach to screen and plan falls interventions focused on deprescribing.

**AIM 2:** Develop and implement a proactive deprescribing medication guidance document with supporting resources (toolkit) for older adults on opioids and/or BZDs.

**AIM 3:** Evaluate (a) the utilization of the deprescribing toolkit in practice; (b) the satisfaction of clinic teams with the toolkit; (c) the impact of the toolkit on opioid and BZD exposure (primary outcome variable); (d) the rate of falls (secondary outcome variable).

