### **5 SCREENING AND MONITORING EVALUATIONS AND MEASUREMENTS (how measurements will be made)**

In addition to the focus group instruments and web-based surveys, the development of which are detailed in Section 3, the following outcomes will be used for the cluster-randomized trial.

**The primary outcome for this study is opioid and BZD exposure, as measured by dose and discontinuation rate. A secondary outcome variable is the rate of falls.** We will also evaluate providers' satisfaction with the deprescribing toolkit. For clinicians providing services at an Intervention Group clinic, we will assess three outcome variables that reflect the process of service delivery: (1) whether or not their patients received education on opioids and BZD and their relationship to falls; (2) whether or not the deprescribing toolkit was utilized as part of the deprescribing process; and (3) whether or not HCPs referred to deprescribing toolkit recommendations concerning medication and non-medications to reduce the patient's risk of falls.

➤ **Opioid and BZD Exposure:** The primary outcome of this study will be exposure to opioid and/or BZD. This will be measured in two ways: (1) dose and (2) discontinuation. We will convert all opioid prescriptions to morphine milligram equivalents (MME), and all BZD prescriptions to diazepam milligram equivalents (DME). The method for calculating MME is well-established, and recommended by the CDC for evaluating opioid-related complications. Calculating DME is analogous, and has been used in previous work to evaluate exposure to BZD and has been used previously to evaluate success of discontinuation interventions. For each class of medications, we will calculate milligram equivalents for all observable prescriptions in the 12 months prior to the index and in the 12 months

post-index. To create a more conservative estimate of the impact of the intervention, we will assume that any authorized refills were filled. [DATA SOURCE: Epic EHR]

Discontinuation will be defined as a lack of opioid or BZD prescription from 181 to 360 days after the index. It is acknowledged that the intervention may not have an immediate impact on opioid and BZD discontinuation as prescribers taper patients' doses down, therefore a gap is given to allow for tapering in advance of discontinuation. [DATA SOURCE: Epic EHR]

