➤ **Risk of Falls:** The secondary outcome of this study will be patients' falls risk, as identified by patients' recorded responses to the STEADI questions embedded in the EHR and by the rate of falls during the one-year post-intervention period compared to the one-year pre-period. We will obtain information regarding falls using data from Epic EHR, and research team members will record the number of injurious falls-related visits made during pre-intervention and post-intervention periods. [DATA SOURCE: Epic EHR]

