## 6 STATISTICAL CONSIDERATION

Statistical considerations are described below for the primary and secondary outcomes from the cluster-randomized trials. No statistical analysis will be conducted with focus groups, and the surveys will be analyzed using descriptive statistics and bivariate assessments for pre-post change in provider knowledge, skills, and attitudes in management of opioids and BZDs between intervention and control clinics.

All hypothesis tests that are observed and deemed to be not statistically significant will be reported as being inconclusive. All statistical estimates of population parameters will be tabulated along with corresponding confidence intervals (CIs) and/or standard errors (SE). All hypothesis tests and tests for power are two-sided with an overall alpha of 0.05, unless otherwise specified.

**6.1 Primary Outcomes: Opioid and BZD exposure,** as defined by changes in milligram equivalents over time across control and intervention groups as well as discontinuation of opioids or BZDs. Outcomes are described in more detail in Section 6.3.

**6.2 Secondary Outcomes: Risk of Falls,** as defined by differences in rate of falls over time across control and intervention groups and described in more detail in Section 6.3.

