**Secondary Analyses:** Our secondary hypothesis is:

- Relative to individuals in both control groups, individuals in both intervention groups will experience a reduction in the risk of experiencing a fall following the index date.

Risk is operationalized as the odds of experiencing a fall in the 12-month post-index compared to the 12 months pre-index. The models used for this analysis match those in Equation 1, with the exception that the models for fall risk will use a log link with a binomial distribution instead of an identity link with a normal distribution.

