## **8 DATA COLLECTION AND MANAGEMENT**

Data collection and management of focus group and web-based survey data are described in Section 3. Additionally, data will be held in a password-protected folder on a shared drive accessible to all members of the study team involved with analysis and interpretation of focus group results.

For the cluster-randomized trial, data for the primary and secondary analyses will be gathered from the EHR at baseline and after the 1-year intervention. The primary and secondary outcomes are observational and do not require direct data collection from patients and providers. All information needed for these analyses will be recorded as a part of usual care. Data will be stored on a secure, HIPAA-compliant research workspace managed by Research Computing, a division of UNC Information Technology Services (ITS). The server requires an ONYEN and a two-factor authentication to log on, which is managed by ITS. There are two level of users, Level 1 and Level 2. Level 1 users will have access to all identifiable data, and Level 2 will have access only to coded datasets.

Identifiable data will be collated by the Carolina Data Warehouse for Health (CDWH) and loaded onto the server by a member of the study team, [name], PhD. All data from CDWH will be received as comma-separated values (CSV) files and will be converted into SAS databases when loaded onto the secure server. He will replace any personal identifiers (e.g. medical record number, beneficiary ID number, name, etc.) with a randomly generated patient ID specific to the study. He will load data into a folder accessible to lower-level users who cannot access or view the fully identified files. All users will be limited to members of the study team and will include only those members who need to analyze or interpret data. [name], PhD will lead the analysis, with support by [name], MS and [name], PhD.

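### The secondary outcome is named as a rate of falls and recorded as a visit count, but the planned binomial model analyses whether any fall occurred and estimates no rate

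*Protocol*

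**What the plan says.** Aim 3(d) and Section 2.2 make the rate of falls the secondary outcome. Section 5 repeats it: "A secondary outcome variable is the rate of falls". Its falls paragraph measures the outcome partly by STEADI responses, which I leave aside, and partly "by the rate of falls during the one-year post-intervention period compared to the one-year pre-period". Section 6.2 gives the definition "as defined by differences in rate of falls over time across control and intervention groups" and refers to Section 6.3 for detail.

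The data item comes from the Epic EHR: "research team members will record the number of injurious falls-related visits made during pre-intervention and post-intervention periods".

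The analysis in Section 6.3 is: "Risk is operationalized as the odds of experiencing a fall in the 12-month post-index compared to the 12 months pre-index". The models follow Equation 1, except that they "will use a log link with a binomial distribution instead of an identity link with a normal distribution".

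On who records the visits, Section 5 says only that they belong to the research team. Section 8 describes coding for lower-level users: "He will replace any personal identifiers (e.g. medical record number, beneficiary ID number, name, etc.) with a randomly generated patient ID". It does not say whether clinic or arm is hidden.

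**The concern.** One label covers three quantities: a rate of falls, a number of visits for injurious falls, and the occurrence of at least one fall in 12 months. They answer different questions. A patient who goes from three falls before index to one after it has improved by any reading of a rate, yet scores yes in both periods. The trial would then report on its secondary outcome without estimating it.

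Two further gaps follow from the same text. A visit is not a fall, and nothing ties several visits for one injury to one event. Under the yes/no analysis this matters at the index date: a visit after index for an injury before it makes the patient a post-index faller. Second, the effect measure is called odds, but the stated link does not give an odds ratio, so the reported number could be mislabelled.

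Section 5 also describes no masking for the recording of visits, in a trial where part of the study team helps to deliver the intervention.

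**Working it through.** The protocol gives no figure to reproduce: Section 6.4 covers power for opioid and BZD dose and discontinuation, and nothing for falls. The check is on the text, followed by an illustration under stated assumptions.

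**1. The quantities side by side**

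| Where | Quantity | Type |
|---|---|---|
| Aim 3(d), 2.2, 5, 6.2 | Rate of falls | Events per time |
| 5 (data item) | Visits for injurious falls | Count of visits |
| 6.3 (text) | Odds of a fall in 12 months | Yes/no |
| 6.3 (model) | Binomial, log link | Risk ratio |

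The yes/no collapse is not spelled out. It is the natural reading of odds of experiencing a fall together with a binomial distribution. With a log link, exp(β3) in Equation 1 is a ratio of risk ratios: post versus pre, intervention versus control. It is neither an odds ratio nor a rate ratio.

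**2. What a rate effect looks like after the collapse**

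Assumptions: falls per patient-year follow a Poisson (k = 0) or negative binomial distribution (dispersion k = 1 or 3). The arms are equal before index and control does not change, so exp(β3) equals the post-index risk ratio. The any-event proportion p0 is 5%, 10% or 25%. Section 1.3 gives one in four older adults falling each year as background; 5% and 10% are assumed for injurious visits. The true rate ratio is 0.70.

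- p(μ) = 1 − exp(−μ) for k = 0
- p(μ) = 1 − (1 + kμ)^(−1/k) for k > 0
- Solve p(μ) = p0 for μ, then p1 = p(0.70 μ)
- Risk ratio = p1/p0; odds ratio = [p1/(1 − p1)] / [p0/(1 − p0)]

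Worked case, p0 = 0.25, k = 0: μ = −ln(0.75) = 0.288; p1 = 1 − exp(−0.201) = 0.182; risk ratio = 0.182/0.25 = 0.730.

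| p0 | k | μ | Risk ratio | Odds ratio |
|---|---|---|---|---|
| 5% | 0 | 0.051 | 0.705 | 0.695 |
| 5% | 1 | 0.053 | 0.711 | 0.700 |
| 5% | 3 | 0.055 | 0.721 | 0.711 |
| 10% | 0 | 0.105 | 0.711 | 0.689 |
| 10% | 1 | 0.111 | 0.722 | 0.700 |
| 10% | 3 | 0.124 | 0.742 | 0.721 |
| 25% | 0 | 0.288 | 0.730 | 0.669 |
| 25% | 1 | 0.333 | 0.757 | 0.700 |
| 25% | 3 | 0.457 | 0.803 | 0.754 |

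A 30% rate reduction shows as a 26% to 30% risk reduction at 5% to 10% (1 − 0.742 = 0.258; 1 − 0.705 = 0.295). At 25% it shows as 20% to 27% (1 − 0.803 = 0.197; 1 − 0.730 = 0.270). The odds ratio differs from the risk ratio in every row, most at 25%, so the label matters.

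**3. An effect on repeat falls only**

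Assume 25% fallers in both arms, with 1.8 falls per faller in control and 1.3 in intervention. Rate ratio = (0.25 × 1.3)/(0.25 × 1.8) = 0.325/0.450 = 0.722. Any-fall risk ratio = 0.25/0.25 = 1.0. The planned analysis would see nothing.

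**4. Observed time**

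Section 6.4 assumes 20% attrition. The yes/no outcome treats a patient who leaves during the post-index year without a recorded fall like one followed to its end. An offset for time corrects this; the model in Section 6.3 has none.

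**5. Masking**

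Section 3.1.3 has study team members working with intervention clinics on implementation. Section 4.2(1) gives the allocation to the study coordinators. Section 6.6 addresses bias in measuring outcomes, but the only design element it names is the pre-post design. No passage says whether the recorders know the arm, or whether recording is manual review or code-based extraction.

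**The case against.** The protocol heads this outcome as risk of falls in Sections 5 and 6.2, refers to 6.3 for detail, and 6.3 expressly operationalises it. It uses the word rate loosely elsewhere: the discontinuation rate is also a yes/no outcome. Both windows are nominally 12 months, and if injurious visits are uncommon and seldom recur, little is lost. Code lists and the length of any episode window belong in a statistical analysis plan, which is not shown. The outcome is secondary, and renaming it would remove the contradiction.

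Much of this limits the size of the point. It does not remove it. Section 6.2 uses rate as the definition, Section 5 collects a count, and Section 6.3 uses neither. Renaming would make the text consistent but would still discard repeat falls already recorded.

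Three stronger readings are tempting and not supported:

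- **That the recorders are unmasked or favour the intervention.** The protocol is silent. It does not say that those who record visits are those who deliver the intervention, and the outcome information comes from routine records.
- **That follow-up in intervention clinics inflates fall visits.** The follow-up in Section 4.2(5) is timed to the deprescribing strategy, not to fall injury.
- **That several visits per fall inflate the analysed outcome.** Within one period they cannot change a yes/no score, and in a count model a multiplier common to arms and periods cancels from the ratio. Only visits that cross the index date matter for the yes/no outcome. How many do so is unknown, and nothing shows that the share differs by arm.

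**Conclusion.** The inconsistency is in the protocol's own text and should be resolved. As written, Section 6.3 does not estimate the rate of falls that Aim 3(d) and Section 6.2 name. It drops repeat events, ignores observed time and attaches the word odds to a model that gives a risk ratio.

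The consequence runs from small to material. At an any-event proportion of 5% to 10%, a rate ratio of 0.70 is only slightly weakened. At 25% with strong overdispersion it reaches 0.803, and an effect confined to repeat falls disappears. These figures rest on the assumed distributions and proportions above, because the protocol gives no frequency for injurious fall visits. They describe a change in what is estimated and some dilution; they do not measure bias between arms.

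On masking, the supportable statement is that none is described. Its importance depends on how much judgement the recording needs, which the protocol does not say.

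**What to change.** In Section 6.3, analyse the number of injurious-fall episodes per observed person-time with a count GEE (Poisson or negative binomial, log link, log of observed time as offset) and the same period-by-arm interaction. Exp(β3) is then a ratio of rate ratios, which matches the named outcome. Count visits for the same injury once, including when they fall on both sides of the index date.

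Keep any injurious fall (yes/no) as a supportive analysis, reported as a risk ratio if the log link stays. Use the term injurious falls throughout, since falls without a recorded visit are not captured by the visit count.

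State that any manual classification of visits is done with clinic and arm removed.

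The cost is small. Visit counts are already to be collected, and PROC GENMOD, named in Section 6.3, fits these models. What is added is a model line, a rule for combining visits, a definition of observed time and one hidden field wherever manual review occurs. The code list and window length can go in the statistical analysis plan. The downside is that a new fall inside the combining window may be missed.

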## 6 STATISTICAL CONSIDERATION

Statistical considerations are described below for the primary and secondary outcomes from the cluster-randomized trials. No statistical analysis will be conducted with focus groups, and the surveys will be analyzed using descriptive statistics and bivariate assessments for pre-post change in provider knowledge, skills, and attitudes in management of opioids and BZDs between intervention and control clinics.

All hypothesis tests that are observed and deemed to be not statistically significant will be reported as being inconclusive. All statistical estimates of population parameters will be tabulated along with corresponding confidence intervals (CIs) and/or standard errors (SE). All hypothesis tests and tests for power are two-sided with an overall alpha of 0.05, unless otherwise specified.

**6.1 Primary Outcomes: Opioid and BZD exposure,** as defined by changes in milligram equivalents over time across control and intervention groups as well as discontinuation of opioids or BZDs. Outcomes are described in more detail in Section 6.3.

**6.2 Secondary Outcomes: Risk of Falls,** as defined by differences in rate of falls over time across control and intervention groups and described in more detail in Section 6.3.

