| Study Rationale                                              | Falls among older adults in the US account for 2.8 million injuries, 800,000 hospitalizations, and 28,000 deaths per year.  US medical costs associated with falls now total approximately \$50 billion.  More than 150 randomized trials document successful falls interventions.  Observational studies show consistent associations between falls and both opioids and benzodiazepines (BZD). Thus, it is widely accepted that fall-related morbidity and mortality could be reduced if systems were in place to identify and intervene in falls risk. Unfortunately, most physicians do not routinely screen older patients for falls  and with the shortage of physicians going into primary care, it is unlikely that screening will improve. Therefore, an educational intervention supporting screening for risk of falls and deprescribing of opioids and benzodiazepines may have a meaningful impact on the fall risk in an elderly population. |
| Study Objective(s)                                           | 
AIM 1: Use EHR data to inform outpatient clinics of older adults who are at high risk of falls due to the chronic use of opioids and/or BZDs. Once alerted, clinics will use a team-based approach to screen and plan falls interventions focused on deprescribing.
 
AIM 2: Develop and implement a proactive deprescribing medication guidance document with supporting resources (toolkit) for use with older adults on opioids and/or BZDs.
 
AIM 3: Evaluate (a) the utilization of the deprescribing toolkit in practice; (b) the satisfaction of clinic teams with the toolkit; (c) the impact of the toolkit on opioid and BZD exposure (primary outcome variable); (d) the rate of falls (secondary outcome variable).
                                                                                                                                                                                                                                      |

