**Cluster-Randomized Trial:**

- Primary: Longitudinal pre-post analysis to detect impact of program on dose of opioid and opioid discontinuation
- Secondary: Rate of falls

**Web-based surveys:** Descriptive statistics

---

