### 6.3 Statistical Methods

**Primary Analyses:** We will examine between-group differences in opioid and BZD exposure associated with an increased risk of falls in the intervention and control groups. Analyses will be performed using the following intention-to-treat principle, and index dates for the intervention group will correspond to the date on which they first received any intervention-related clinical activity. Index dates for otherwise eligible patients from the control group will be chosen at random from each patients' set of clinic visits corresponding to an eligible intervention visit during the study period. Our primary hypotheses are:

- Relative to individuals in both control groups, individuals in both intervention groups will experience a significant reduction in the milligram equivalent exposure to opioids and BZDs during the 1-year follow-up period.

- Relative to individuals in both control groups, individuals in both intervention groups will experience a significantly greater discontinuation rate of opioids and BZDs during the follow-up period 181 to 360 days after index.

There are two overlapping groups of patients aged 65+ that will be included in this study: opioid users and BZD users. For each hypothesis, there will be separate models comparing the impact of the program on opioid users and BZD users. Patients who use both will appear in both models. To examine any differential impact of the program among patients who use both classes of medications, a sensitivity analysis will be performed and will include an indicator variable for patients who use both classes.

Generalized estimating equations (GEE, PROC GENMOD) will be used to create longitudinal pre-post model for the milligram equivalent exposure models. An identity link with a normal distribution will be used for milligram equivalent exposure. The functional form of the model is as follows:

$$\text{Eq. 1: } Y = \beta_0 + \beta_1 X_{\text{exp}} + \beta_2 X_{\text{period}} + \beta_3 X_{\text{exp} \times \text{period}} + \beta_n X_n + \epsilon$$

Where  $X_{\text{exp}}$  is the exposure group indicator,  $X_{\text{period}}$  is the pre-post indicator, and  $X_{\text{exp} \times \text{period}}$  is the period-by-treatment interaction indicator and, correspondingly,  $\beta_3$  is the parameter of the difference in outcome by period for the intervention group compared to the control.  $X_n$  represents a vector of covariates.

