### **6.4.3 Milligram equivalent exposure to BZDs**

Effect of various interventions on milligram diazepam equivalent per day exposure to BZDs has shown mean reductions ranging from 25% to 85%. If clinics are randomly assigned to a treatment group and a control group, with an equal number of patients in both groups, a GEE model with a total sample size of 3000 patients, each measured two times before and after intervention, will have statistical power in the range of 0.678-0.969 to detect differences in means of 0.25 or higher in milligram equivalent exposure when the standard deviation is below 2. Pre-period measurements will include the 12-month period prior to index, and post-period measurements will include the 12 months following index. This assumes that the baseline correlation between observations is 0.2 or higher and that we will observe a 20% attrition rate. Power increases for larger mean difference values and drops significantly at higher standard deviation values.

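### The protocol claims an overall alpha of 0.05 for four primary tests without a split, order or success rule, and its synopsis analytic plan lists only the two opioid tests as primary

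*Protocol*

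**What the plan says.** Section 6 sets the error rate for the whole trial: "All hypothesis tests and tests for power are two-sided with an overall alpha of 0.05, unless otherwise specified".

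Section 5 defines the primary outcome: "The primary outcome for this study is opioid and BZD exposure, as measured by dose and discontinuation rate". Section 6.3 gives two primary hypotheses, one on milligram-equivalent exposure and one on discontinuation, and adds: "For each hypothesis, there will be separate models comparing the impact of the program on opioid users and BZD users". It also says of the two user groups: "Patients who use both will appear in both models". Sections 6.4.1 to 6.4.4 give a separate power statement for each of the four combinations. Section 6.5 plans no interim analysis.

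The synopsis gives the primary set in two ways. Its Statistical and Analytic Plan row reads "Primary: Longitudinal pre-post analysis to detect impact of program on dose of opioid and opioid discontinuation", with no BZD outcome. Its Aim 3(c) has "the impact of the toolkit on opioid and BZD exposure (primary outcome variable", which includes BZD. Sections 2, 2.1, 5, 6.1 and 6.3 agree with Aim 3(c).

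**The concern.** An *overall* alpha is normally read as a limit on the error across a family of tests. Here the family has four members, and nothing in the protocol says how the limit is kept: there is no division of alpha, no order of testing, and no statement of whether one significant result or all four make the trial positive. If a single result suffices and each test is taken at 0.05, the trial can claim primary success under no effect well above 5% of the time.

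The size of the family is also unsettled. By the synopsis analytic plan it is two tests, and by the rest of the protocol it is four. Any adjustment, and any judgement of success, depends on which is meant.

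**Working it through.** **1. Count the primary tests.** Two hypotheses (dose, discontinuation) × two separate models (opioid users, BZD users) = 4. On the synopsis analytic plan alone the count is 2.

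**2. Reproduce the plan's own figure, to see which alpha it carries.** Section 6.4.3 says the design "will have statistical power in the range of 0.678-0.969 to detect differences in means of 0.25 or higher". Inputs from that section:
- difference 0.25
- SD below 2 (limit 2 used)
- correlation 0.2 or higher (limit 0.2 used)
- 3000 patients, equal split, 20% attrition: 3000 × 0.8 / 2 = 1200 per arm

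For a pre-post difference compared between arms:
- SD of change = 2 × √(2 × (1 − 0.2)) = 2.530
- SE = 2.530 × √(2/1200) = 0.1033
- 0.25 / 0.1033 = 2.421
- Power = Φ(2.421 − z), with z the two-sided critical value

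| Two-sided alpha for this test | z | Power |
|---|---|---|
| 0.05 | 1.960 | 0.6775 |
| 0.025 | 2.241 | 0.571 |
| 0.0125 | 2.498 | 0.469 |

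The stated 0.678 agrees with the first row: at the stated limits, this one test was given the full 0.05.

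**3. Chance of at least one false positive if any one result counts, each test at 0.05.**
- Four independent tests: 1 − 0.95⁴ = 0.185. Upper bound under any dependence: 4 × 0.05 = 0.20.
- Correlated tests: the protocol gives no correlations, so a range was assumed: 0 to 0.9 between dose and discontinuation within a drug class, and 0 to 0.5 between classes. Simulation of four z-tests (1,000,000 draws) gave 0.126 to 0.186.
- Opioid pair only: 1 − 0.95² = 0.0975 if independent, and 0.070 to 0.098 over the same range.

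**4. If all four must be significant.** No adjustment is needed. With no effect on any outcome, the simulated chance of all four being significant was about 0.004 at most. Joint power cannot exceed the weakest component, however. The lowest stated values are 0.631 (opioid discontinuation, Section 6.4.2) and 0.678 (BZD dose, Section 6.4.3), so at those lower ends joint power is at most 0.631.

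**5. Effect of an equal split.** Four tests at 0.05 / 4 = 0.0125 give 1 − 0.9875⁴ = 0.0491 if independent, and at most 0.05 in any case. Rescaling the stated BZD figure: Φ⁻¹(0.678) = 0.462, and Φ(0.462 + 1.960 − 2.498) = 0.47. With only the opioid pair primary, 0.05 / 2 = 0.025 each would suffice.

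None of these power calculations allows for clustering by clinic.

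**The case against.** The strongest reply is that multiplicity procedures often sit in the statistical analysis plan, which is not at hand, and that Section 6 leaves room for something to be specified otherwise. This stands as far as it goes: the absence of a named procedure is not, by itself, an error in the protocol. It does not answer the other two points. The protocol itself makes the *overall* claim beside a power figure that matches the unadjusted level, and it names two different primary sets.

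Four stronger readings are tempting, and the document does not support them.

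- *The synopsis as a whole makes only opioid outcomes primary.* It does not. Only its analytic-plan row does; Aim 3(c) includes BZD, so the synopsis contradicts itself.
- *The power figure proves that every test is run at 0.05 and that no adjustment was planned.* No per-test level is written. Section 6.4.3 gives open limits, and 0.678 also results at 0.0125 with correlation about 0.465 and SD 2, or at 0.025 with SD about 1.79 and correlation 0.2. The match at the stated limits is suggestive, not unique. A power calculation at 0.05 also does not settle how the analysis will be done.
- *The error rate is certainly inflated.* That needs a rule under which any one result counts, and the protocol states none. The hypotheses speak of opioids and BZDs jointly and could be read as requiring all four.
- *The stated opioid dose power of 0.865 would fall to 0.71 at 0.0125.* This only rescales a figure that does not reproduce. With difference 0.30, SD 3 and correlation 0.2, the method of step 2 gives SE = 3 × √1.6 × √(2/1200) = 0.1549 and power Φ(0.30/0.1549 − 1.960) = 0.49. It says nothing reliable about the alpha used.

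**Conclusion.** The point holds in a conditional form. The protocol asserts an overall two-sided alpha of 0.05, sets up four primary tests, and contains nothing that delivers that limit. If any one significant result counts and each test is taken at 0.05, the chance of at least one false positive is about 13–19%. The 18.5% figure assumes independence, and the lower values rest on correlations the protocol does not give. If all four must be significant, the 5% limit holds unadjusted, but the four separate power statements then overstate the chance of success, which is capped by the weakest test. Both readings require the protocol to be corrected. The conflict over the primary set is a plain contradiction whatever a separate analysis plan may say. A reader might conclude that the trial's error rate is shown to fail, or that a decision not to adjust has been documented; neither is established.

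**What to change.** 1. State one primary set and use it everywhere: the synopsis analytic plan, synopsis Aim 3(c), and Sections 2, 2.1, 5, 6.1 and 6.3.
2. State the success rule.
   - If any one result can count, control the error across the primary tests by Holm, or by a fixed order set down in advance.
   - Otherwise, state that all must be significant, or replace *overall* with *per-test* so that no family-wise limit is claimed.
3. Restate power in Section 6.4 at the alpha and under the rule actually used. For example, the lower-end BZD dose power of 0.678 becomes about 0.47 at 0.0125, and an all-four rule needs joint power.

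The cost is mainly wording. Holm lowers the stated power; 0.0125 is its strictest step. A fixed order costs the first test nothing, but each later test then depends on the ones before it. An all-four rule leaves alpha untouched and lowers the chance of overall success.
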